## Abstract

**Background:**

Growing evidence suggests that experiences in the early years play a major role in children’s development in terms of health, wellbeing and educational attainment. The Trial of healthy relationship initiatives for the very early years (THRIVE) aims to evaluate two antenatal group interventions, *Enhanced Triple P for Baby* and *Mellow Bumps*, designed for those with additional health or social care needs in pregnancy. As both interventions aim to improve maternal mental health and parenting skills, we hypothesise that in the longer term, participation may lead to an improvement in children’s life trajectories.

**Methods:**

THRIVE is a three-arm, longitudinal, randomised controlled trial aiming to recruit 500 pregnant women with additional health or social care needs. Participants will be referred by health and social care professionals, predominately midwives. Consenting participants will be block randomised to one of the three arms: *Enhanced Triple P for Baby* plus care as usual, *Mellow Bumps* plus care as usual or care as usual. Groups will commence when participants are between 20 and 34 weeks pregnant.

**Discussion:**

The population we aim to recruit are traditionally referred to as “hard to reach”, therefore we will monitor referrals received from maternity and social care pathways and will be open to innovation to boost referral rates. We will set geographically acceptable group locations for participants, to limit challenges we foresee for group participation and retention. We anticipate the results of the trial will help inform policy and practice in supporting women with additional health and social care needs during antenatal and early postnatal periods. This is currently a high priority for the Scottish and UK Governments.

**Trial registration:**

International Standard Randomised Controlled Trials Number (ISRCTN) Registry, ISRCTN:21656568. Registered on 28 February 2014 (registered retrospectively (by 3 months)).

**Electronic supplementary material:**

The online version of this article (10.1186/s13063-019-3571-5) contains supplementary material, which is available to authorized users.

## Background

Emerging neuroscience evidence suggests that the interactions between a child and their mother, particularly from conception to age 3 years, greatly influence the development of the child’s “base for competence and coping skills that will affect learning, behaviour and health throughout life” [1]. Women with additional health and social care needs in pregnancy (for instance, due to domestic abuse, mental health problems, an addiction, having been in state care, etc.) are likely to be more anxious, depressed and have higher levels of circulating stress-related hormones [2], which can (1) create adverse epigenetic modifications to the developing foetus that permanently affect the baby’s response to stress [3, 4] and (2) independently disrupt the mother’s ability to be sensitive to her baby [5]. Both these pathways may adversely affect the mother-infant interaction. In addition, both poor mother-infant interaction and maternal mental ill health strongly predict child maltreatment [6, 7] and a disadvantaged trajectory for children in terms of their future social, emotional and cognitive development and health [8–10]. Thus, postnatal interventions may not be able to undo all of the changes resulting from maladaptive coping in adverse circumstances during pregnancy.

Sensitive mother-infant interactions are characterised by reciprocal communication from an early stage, which facilitates language but also significantly reduces the risks of maltreatment. This is thought to be due to mothers perceiving their infants as co-operating with them [11]. Mother-infant interactions that succeed in facilitating secure future attachments enable overall development, including language, and may set infants onto a more positive life trajectory. The evidence for the effect of early child development on health and wellbeing in later life is widely accepted and early childhood interventions, such as the High/Scope Perry Preschool Project [12], the USA Family Nurse Partnership (FNP) [13], the Carolina Abecedarian Project [14] and the Chicago Child-Parent Programme [15], have had positive effects on a number of child development domains and on wellbeing and life success in adulthood. Furthermore, early intervention, is generally more cost-effective than intervening later, and is most effective in the antenatal period [16]. However, many applied economic evaluations in the area of home visiting and parenting have had diverse economic objectives and methodological problems including the lack of a societal perspective and limited cost analysis.

We hypothesise that the provision of a parenting support intervention, *Enhanced Triple P for Baby* (ETPB) or *Mellow Bumps* (MB), in addition to routinely provided care during the antenatal and early postnatal phase, will be a cost-effective way of improving maternal mental health, increasing the dyadic synchronicity and sensitivity of mother-infant interactions, reducing the risk of child maltreatment and improving child language and socio-emotional development. The Trial of healthy relationship initiatives for the very early years (THRIVE) is a three-arm, randomised controlled trial of women with additional health and social care needs in pregnancy aiming to compare ETPB plus care-as-usual (CAU) or MB plus CAU with CAU. Based on recent economic evaluation research carried out on a similar trial in Oxfordshire [17, 18], THRIVE will include a comprehensive economic evaluation.

The primary research questions that will be addressed by THRIVE are:
Do participants receiving ETPB plus CAU or MB plus CAU have significantly lower anxiety, depression and outwardly directed irritability compared with those receiving CAU alone when their infants are around 6 months old?Do participants who receive ETPB plus CAU or MB plus CAU have more sensitive interactions with their infants compared with those receiving CAU alone when their infants are around 6 months old?

The secondary research questions that will be addressed by THRIVE are:
Do infants whose parent(s) receive ETPB plus CAU or MB plus CAU show more cooperative behaviour signs than those whose parent(s) received CAU alone?Do ETPB or MB lead to changes in the number of children flagged as “at risk” on the social services risk register, under a child protection plan, taken into local authority care or attending an accident and emergency department?Do ETPB or MB lead to improvements in the socio-emotional development of children around 30 months old?Do ETPB or MB lead to an improvement in language development in children around 30 months old?Do ETPB or MB lead to an improvement in longer-term educational and health outcomes for children?Is either ETPB or MB cost-effective for the National Health Service (NHS) or society more broadly, in the long term?Do differences in programme fidelity, practitioners’ characteristics and motivation, mothers’ engagement, the intervention mechanisms and contextual factors affect mother and infant outcomes?Does fathers’ involvement or support affect mothers’ engagement with ETPB or MB?How do participants’ experiences of being parented influence their own parenting values and behaviour?

## Methods

THRIVE is a three-arm, randomised controlled trial of 500 participants with additional health and social care needs in pregnancy, classified by National Health Service Greater Glasgow & Clyde (NHS GGC) Special Needs in Pregnancy service (SNiPs) protocol [19] (e.g., domestic violence, mental illness, a history of substance misuse, being looked after in local authority care or criminal justice involvement). Consenting participants will be randomly allocated to one of the three trial arms: ETPB plus CAU, MB plus CAU or CAU alone. All participants and their infants will continue to receive their antenatal and postnatal CAU according to local NHS and local authority guidelines.

THRIVE is sponsored by NHS GGC Health Board (Reference GN12KH589; NHS Greater Glasgow & Clyde, Research and Development Management Office, West Glasgow Ambulatory Care Hospital, [name]), which is responsible for ensuring that THRIVE is managed “according to the Research Governance Framework for Health and Community Care (Second edition, 2006) and World Medical Association Declaration of Helsinki Ethical Principles for Medical Research Involving Human Subjects”. The study is subject to audit by the NHS GGC Health Board at any time during the trial. In addition, the University of Glasgow Medical Research Council/Chief Scientist Office Social and Public Health Science Unit (MRC/CSO SPHSU) has standard operating procedures that include auditing of ongoing studies.

### Inclusion criteria

Pregnant women aged 16 years and older (or 14 years and older with social work support) who meet the SNiPs criteria, have capacity to consent and are living within the geographical areas of NHS GGC and NHS Ayrshire & Arran (NHS A&A) will be invited to take part in THRIVE when they are between 8 and 24 weeks pregnant. The trial team will use a variety of methods to maximise participant recruitment into the trial:
Patients within NHS GGC will be routinely asked if their information can be passed onto researchers. If a pregnant women assents, a THRIVE researcher will contact her to discuss the trial, screen for eligibility and seek consent to recruit to the trial.Participants will be referred by their health or social care practitioner(s) to the research team.Members of the THRIVE team will attend antenatal clinics in hospital and community settings to meet with pregnant women. Participants will be screened by researchers for eligibility.Targeted advertisements, including web-based content, will be used to recruit participants via community centres, health centres, local classified sites, social media and parenting forums. Interested parties will be screened for eligibility by members of the research team.

Following informed, written consent to participate in the trial (Additional file 1), participants will be asked to complete baseline measures after a viable pregnancy has been confirmed through medical records, around the 12th week of pregnancy.

### Exclusion criteria

The following participants will be excluded from the trial:
Women with difficulties in speaking or comprehending English, because this can limit their ability to engage in group sessions.Women with no fixed abode, because it may be difficult to trace and retain them within a longitudinal study.Women experiencing active psychosis, because this illness can limit their ability to engage in group sessions.Women for whom it is known during pregnancy that their child will be removed at birth, because doing so may make the separation more difficult.

Advice about the suitability of potential participants to participate in the trial will be sought from the referring health or social care practitioners.

### Interventions

#### Enhanced Triple P for Baby (ETPB)

ETPB, informed by social learning theory, is an intervention designed to facilitate a smooth transition to parenthood for expectant parents by reducing the impact of known risk factors for perinatal distress and difficulties. It aims to provide infants with a healthy start to life by offering parenting skills training as well as psychological coping skills training to parents to enhance parental and infant wellbeing. In addition to focusing on practical parenting and coping skills, group sessions encourage participants to work with their partner or a supportive individual to develop and explore strategies needed to maintain more harmonious family relationships. Each participant’s partner or supportive other is invited to all of the group sessions but participants without support are not excluded. The programme offers four 2-h antenatal group sessions in a community setting and up to three individual 1-h postnatal sessions delivered face-to-face in the woman’s home. The programme is completed with a final 2-h postnatal group session. Antenatal sessions are scheduled to begin before the woman is 34 weeks pregnant, and the postnatal sessions are delivered after their infant is 6 weeks old. ETPB was developed at the Parenting and Family Support Center at the University of Queensland, Australia. Triple P interventions, provided by Triple P International (http://www.triplep.net), are delivered to parents in five different levels of intensity, the efficacy and effectiveness of which have been cited in numerous studies and randomised trials [20, 21]. More recently, however, there has been a call for more registered independent trials (with pre-specified main outcomes), such as THRIVE [22].

#### Mellow Bumps (MB)

MB is underpinned by attachment theory and aims to encourage nurturing and attuned relationships between the mother and developing infant. MB is intended to decrease maternal antenatal stress levels, increase expectant mothers’ understanding of the neonates’ capacity for social interaction and emphasise the importance of early interaction in enhancing brain development and attachment. Participants are encouraged to identify potential sources of stress and work through how to manage these, reflect upon and identify sources of positive social support and to identify barriers to good parenting. The programme offers seven 2-h antenatal group sessions and one 2-h postnatal group session. Antenatal sessions begin when participants are between 20 and 30 weeks pregnant, and the postnatal sessions are delivered when infants are between 6 and 12 weeks old. Partners and/or supportive others are invited to attend one antenatal session. MB was developed by a charity, Mellow Parenting (http://mellowparenting.org), based in Govan, Glasgow. Evidence for Mellow Parenting programmes is small-scale but encouraging [23–25].

#### Care-as-usual (CAU)

All participants in this study will continue to receive their routine antenatal and postnatal care. Generally, this involves care from hospital and community-based healthcare specialists, such as midwives, obstetricians and health visitors. The exact care received by each participant will depend on their individual additional health and social care needs and may also engage services from other sources including social work services and voluntary agencies. All care received will be in line with local authority and Government policy and guidelines [19, 26–30]. The specific services accessed by each participant as part of their CAU will be captured in service use diaries.

Participants randomised to the CAU arm of the trial will not be offered either intervention (ETPB or MB) in THRIVE on completion of data collection. However, participants may access Triple P International and Mellow Parenting programs as part of their CAU, where these are offered through social work or third-sector organisations within NHS GGC and NHS A&A. Uptake of other parenting programmes outside of THRIVE will be captured in the service use diary.

### Trial group organisation

Post randomisation the group sessions will be organised by administrative staff within the trial research team and delivered in community settings, such as local supermarket community rooms or hospital antenatal education rooms. A taxi service will be provided, first, to ensure safe transport of participants to and from the group venue sessions and second, with the aim of reducing anticipated transportation barriers and thereby supporting attendance. The trial administrator will contact participants by phone or text to invite them to sessions, with reminders sent on the day of each group session to maximise group attendance. Attendance at each session will be recorded in an attendance register by group facilitators.

Participation in all aspects of THRIVE will be voluntary, and some participants may choose not to attend any or to attend only some of the group sessions. In these situations, the research team will seek to record the reason for non-attendance. For MB, participants who do not attend either of the first two group sessions will not be invited to subsequent sessions, but will still be eligible for follow-up data collection. For ETPB, participants will be invited to all antenatal group sessions regardless of attendance at previous sessions.

THRIVE group facilitators will be independent of the trial, have a variety of health and social care professional backgrounds, and be employed by NHS GGC and NHS A&A. In order to avoid contamination between intervention arms in the trial group, facilitators will be randomly allocated to deliver only one intervention, the only exception being those with prior knowledge of an intervention - in this instance they will be allocated to deliver that intervention. Training will be conducted by qualified trainers from the host organisation of each intervention.

### Outcome evaluation

Data will be collected at two time points as outlined subsequently.

#### Baseline: 12–24 weeks pregnant

The baseline questionnaire (Additional file 2) will include the following validated measures:
The Brief Symptom Inventory (BSI-53; Question (Q)48 (Additional file 2)), which is a 53-item questionnaire covering nine symptom dimensions: somatization, obsession-compulsion, interpersonal sensitivity, depression, anxiety, hostility, phobic anxiety, paranoid ideation and psychoticism [31, 32]. The Global Severity Index from this scale will be used in randomisation to indicate severity of symptoms.The Hospital Anxiety and Depression Scale (HADS), which is a 14-item questionnaire assessing symptoms of anxiety and depression [33]. This will be enhanced by the 4-item outwardly directed irritability (I) questions adopted from the Adult Wellbeing Scale (AWS) [34], as a baseline measure for the primary outcome of maternal mental wellbeing (Q47).The EuroQol 5 Dimensions (EQ-5D-3 L; Q49), which is a standardized instrument to measure health-related quality of life, which will be used for health economic analyses [35].The 23-item Recent Life Events questionnaire (Q45), to determine the experience of specific events in the past year, and whether these affect the respondent [36, 37].The 12-item attitudes and pregnancy to the baby subscale from the Maternal Attitudes and Maternal Adjustment questionnaire (Q32) [38].The 28-item Childhood Trauma Questionnaire (Q89) as a measure of childhood abuse and neglect [39].

The baseline questionnaire will also include questions assessing reasons for vulnerability in pregnancy; socio-demographic characteristics including age, Scottish Index of Multiple Deprivation, ethnicity, education and employment; previous childbirth history and parity; health in pregnancy; and substance abuse [40].

#### Follow up at 6 months postnatal (primary outcome end point)

The primary outcome of maternal mental wellbeing will be assessed by the HADS+I, included in the follow-up questionnaire (Additional file 3; Q35). The primary outcome of mother-infant interaction quality (MIIQ) will be measured based on the CARE Index Dyadic Synchrony Score [41] determined from an episode of play recorded during the follow-up visit when the infant is around 6 months old.

In addition to the HADS+I, the follow-up questionnaire will include the following listed validated measures that will be analysed as secondary outcome measures:
The 33-item Support and Control in Childbirth Scale will be used to determine the participants experiences during childbirth (Q14) [42].The EQ-5D-3 L will be used within health economics analyses (Q36) [35].The 23-item Recent Life Events questionnaire (Q41) will be used to determine the experience of specific events in the past year, and whether these affect the respondent [36, 37].The 18-item Cognitive Emotion Regulation questionnaire (Q42) will be used to determine cognitive emotion regulation across nine conceptual scales: self-blame, other-blame, rumination, catastrophizing, positive refocusing, planned, positive reappraisal, putting into perspective and acceptance [43].The 18-item partner subscale of the Postpartum Support Scale (Q68) [44] will be used.The 18-item Parental Regulation Inventory will assess the degree to which parents use specific strategies to encourage or discourage their partner to be involved in parenting (Q69) [45].The 12-item marital relationship scale of the Maternal Adjustment and Maternal Attitudes questionnaire (Q70) will be used [38].The 12-item Multidimensional Scale of Perceived Social Support relating to support from a significant other, family and friends will be used (Q87) [46].The 15-item Karitane Parenting Confidence Scale will be used to assess parenting self-efficacy (Q88) [47].The 14-item Maternal Attitudes Questionnaire will be used to assess attitudes towards motherhood across three domains: expectations of motherhood, expectation of self as a mother and role conflict (Q89) [48].The Parent Coping Scale, a single question will be used to provide a global measure of coping with being a parent (Q92) [49].The 43-item Infant Crying Questionnaire will be used to assess participants’ thoughts/feeling towards infant crying and how they would respond (Q93 and Q94) [50].We will use 16 items from the Postpartum Bonding questionnaire to assess the quality of the mother’s relationship with her baby (Q96) [51].

During the follow-up visit permission will be sought to video-record mother and child interactions around one episode of play and one episode of care, such as feeding or nappy changing. MIIQ will be rated by two research assistants at The University of Manchester (UoM) who will be blinded to the trial arm allocation ensuring single-blind evidence of the effectiveness of the interventions on MIIQ. MIIQ will be measured using both the CARE Index Dyadic Synchrony Score (primary endpoint) [41] and the Mellow Parenting Observation System (MPOS) [52]. As part of this process inter-rater reliability will be established.

As the target population of this study is traditionally seen as “hard to reach”, a number of strategies will be undertaken in order to obtain follow-up data from as many participants as possible, including the offer of £15 vouchers for completed follow-up questionnaires, contact by phone, email and text to arrange follow-up data collection appointments, confirmation of current contact details with the NHS Clinical Research Facility and sending out congratulations cards at birth with a reminder to inform research staff of changes in contact details.

### Economic Evaluation

The economic evaluation will assess the implementation costs, resource use and outcomes associated with each intervention and CAU from the NHS and Personal Social Services (PSS) perspective favoured by the National Institute for Health and Care Excellence (NICE). A broader societal perspective will also be adopted to allow for the possibility of costs and outcomes arising beyond the NHS and PSS, such as housing, education, employment and justice. To facilitate measurement of data on resource use, all participants will be asked to keep a service use diary recording attendance at NHS, social care, local authority and voluntary organisations for both mother and child. The diary will be used as an aide memoir to collect mother and child data between baseline and follow up, and will be used to measure additional and unintentional cost burden/savings associated with the intervention. Participants will additionally be asked to complete a health and social care resource-use questionnaire at follow up based on the same information as the diary.

Up-to-date unit costs will be attached to quantities of resource use to generate mean costs per study participant. The incremental costs and benefits of the treatment arms compared with CAU will be reported within an incremental cost-effectiveness ratio (ICER) if appropriate. The inclusion of the EQ-5D generic outcome measure [35] will also allow the estimation of quality-adjusted life years (QALYs) facilitating cost-utility analysis, the preferred evaluative technique of NICE. Sensitivity analysis will be carried out on the perspective adopted and the key cost-drivers and outcomes. As per recent economic evaluation guidance, missing data will be predicted as a function of relevant baseline covariates [53].

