### Statistical analysis

THRIVE has been powered based on the primary outcome measure of maternal mental wellbeing. The efficacy of ETPB and MB will be analysed at a significance level of 2.5% in order to maintain an overall type I error rate of 5%. Two analyses, performed in a hierarchical fashion so that no further *p* value adjustment is necessary, will be undertaken. In analysis 1, the combined intervention groups (ETPB and MB) will be compared with CAU. If analysis 1 detects a difference at a 2.5% level of statistical significance, analysis 2 will compare ETPB with MB as a primary analysis, to be judged at a 2.5% statistical significance level. If analysis 1 does not yield a statistically significant result, then analysis 2 will be considered a secondary analysis.

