#### Power calculation

In order to have 90% power to detect an effect size of 0.4 for Analysis 2 (ETPB versus MB) 157 participants are required in both the ETPB plus CAU and MB plus CAU groups. Comparing these 314 participants with CAU alone in analysis 1 (ETPB and MB vs CAU), requires 61 participants in the CAU alone group to achieve 90% power. Therefore, 375 participants are required in a ratio of ETPB:MB:CAU of approximately 5:5:2. To allow for 25% attrition at follow up, 500 participants will be recruited and randomised.

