#### Planned analysis

Baseline-adjusted linear regression analysis (analysis of covariance) will be used to compare primary statistical outcomes between intervention groups. Similar methods will be used for other outcomes (using data transformation and alternative regression methods, depending on the distribution of each outcome). Regression models will be extended to investigate the effects of baseline characteristics and the potential moderating effects of these variables and other measures of intervention compliance. Repeated measures methods will be applied to outcomes collected at more than one post-baseline assessment.

For participants discontinuing from the study before the postnatal follow-up data collection, baseline data will continue to be analysed when consent is provided. Missing values will not be imputed. The sensitivity of the primary outcome analysis to missing values will be explored using multiple imputation, generating 10 imputed data sets, using all available data to predict missing values. Analyses will be conducted for the intention-to-treat population, consisting of all participants who have been randomised to the trial. In addition, analyses will also be undertaken for the per-protocol/on-treatment population.

For the economic analysis the incremental costs and benefits in each treatment arm will be reported within an incremental cost-effectiveness ratio (ICER) if appropriate. Within-trial analysis of costs and effects will be undertaken in STATA (StataCorp, TX, USA), adhering to good practice for economic evaluations alongside clinical trials [58, 59]. Missing data will be explored by employing multiple imputation methods using alternative configurations of baseline covariates [53, 60]. Based on the availability of linked routine data, longer-term costs and outcomes will be assessed by linking short-term outcomes identified in the study to potential longer-term impacts on health and wellbeing for both mother and infant, via trial extrapolation methods including economic modelling techniques.

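### The ICERs are planned against CAU alone, with no ETPB–MB cost-effectiveness comparison, so they cannot show which programme is the better buy if both look acceptable

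*Protocol article*

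**What the plan says.** The Methods section sets up three alternatives: "Consenting participants will be randomly allocated to one of the three trial arms: ETPB plus CAU, MB plus CAU or CAU alone". The Economic Evaluation section says that "The economic evaluation will assess the implementation costs, resource use and outcomes associated with each intervention and CAU", so costs and outcomes will exist for every arm. It then fixes the comparator: "The incremental costs and benefits of the treatment arms compared with CAU will be reported within an incremental cost-effectiveness ratio (ICER) if appropriate".

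The Planned analysis section repeats the intention without naming a comparator: "For the economic analysis the incremental costs and benefits in each treatment arm will be reported within an incremental cost-effectiveness ratio (ICER) if appropriate". It adds that the within-trial analysis will be done "adhering to good practice for economic evaluations alongside clinical trials".

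The economic question, among the secondary questions in the Background, is: "Is either ETPB or MB cost-effective for the National Health Service (NHS) or society more broadly, in the long term".

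On the clinical side the two programmes are compared directly. If analysis 1 is significant, "analysis 2 will compare ETPB with MB as a primary analysis, to be judged at a 2.5% statistical significance level". The trial is sized for that contrast: "In order to have 90% power to detect an effect size of 0.4 for Analysis 2 (ETPB versus MB) 157 participants are required" in each programme arm.

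**The concern.** A payer can give a woman ETPB, MB or neither, so these are three mutually exclusive options. With three such options, ratios against one shared comparator do not identify the best one. The dearer programme has to justify its extra cost by its extra benefit over the next-best option that is not dominated, and that option may be the other programme rather than CAU.

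Under the comparator stated, the question whether either programme is cost-effective can be answered with both. A reader choosing between them would then lack the comparison that decides the choice, with its uncertainty. The article expects its results to inform policy, so that choice is a realistic use of the findings.

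**Working it through.** **No plan figure to reproduce.** The article gives no ICER, cost, QALY gain or threshold. The check is therefore on the text, followed by the logic with assumed figures.

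**Step 1: what the text covers.** The economic material is in the Background, Economic Evaluation, longer-term follow-up, Planned analysis, Discussion and registration table. CAU is the only ICER comparator named in any of them. None mentions an ETPB–MB cost-effectiveness increment, an ordering of the three options, a dominance check or net benefit across the arms.

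**Step 2: is a cost difference between the programmes likely?** From the Interventions section:
- ETPB: 4 × 2 h antenatal + 1 × 2 h postnatal = 10 group hours, plus up to 3 × 1 h = 3 individual home hours.
- MB: 7 × 2 h antenatal + 1 × 2 h postnatal = 16 group hours.

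The formats differ, so a cost difference is likely. Without unit costs or group sizes its direction cannot be established.

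**Step 3: the mechanism.** Write ΔC and ΔE for a programme's extra mean cost and QALYs over CAU, and λ for the threshold.
- ICER against CAU = ΔC/ΔE.
- Head-to-head ICER = (ΔC₂ − ΔC₁)/(ΔE₂ − ΔE₁), where programme 2 is the dearer.
- Net monetary benefit (NMB) = λΔE − ΔC.

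The results conflict when both programmes pass at λ against CAU, but programme 2 fails at λ against programme 1 or is dominated by it. All inputs below are assumptions, and either programme could be the dearer one.

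| Set | Cheaper: ΔC, ΔE | Dearer: ΔC, ΔE | ICER v CAU, cheaper | ICER v CAU, dearer | Dearer v cheaper | Conflict for λ |
|---|---|---|---|---|---|---|
| 1 | £400, 0.030 | £900, 0.040 | £13,333 | £22,500 | £50,000 | £22,500 to £50,000 |
| 2 | £500, 0.05 | £1,000, 0.06 | £10,000 | £16,667 | £50,000 | £16,667 to £50,000 |
| 3 | £500, 0.05 | £900, 0.06 | £10,000 | £15,000 | £40,000 | £15,000 to £40,000 |
| 4 | £500, 0.05 | £700, 0.06 | £10,000 | £11,667 | £20,000 | £11,667 to £20,000 |
| 5 | £500, 0.05 | £900, 0.045 | £10,000 | £20,000 | dominated | above £20,000 |
| 6 | £500, 0.04 | £800, 0.07 | £12,500 | £11,429 | £10,000 | none |

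Set 1 in full: 400/0.030 = 13,333; 900/0.040 = 22,500; (900 − 400)/(0.040 − 0.030) = 50,000. At λ = £30,000, NMB is 30,000 × 0.030 − 400 = £500 for the cheaper programme and 30,000 × 0.040 − 900 = £300 for the dearer. Both pass against CAU, but the cheaper is the better buy. At λ = £20,000 the dearer one already fails against CAU (800 − 900 = −£100), so there is no conflict.

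Set 6 goes the other way. The cheaper programme is extendedly dominated, the dearer has the larger NMB (£600 against £300 at λ = £20,000), and the ratios against CAU point to the same choice.

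**Step 4: precision of the omitted contrast.** Take the planned completers (157, 157 and 61) and assume equal SDs:
- ETPB v MB: SE = SD × √(1/157 + 1/157) = 0.113 SD.
- Either programme v CAU: SE = SD × √(1/157 + 1/61) = 0.151 SD.

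The second is about a third larger. The comparison not planned for cost-effectiveness is the one that the allocation estimates most precisely.

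**The case against.** The strongest reply is that the plan answers the question it asks. The Background hypothesis concerns each programme in addition to routine care, and the economic question is about either programme, not which is better. ICERs against CAU are a legitimate answer to that. This stands, and it is why they should be kept.

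Second, a reader might infer that the plan rules out an ETPB–MB ICER. It does not. It names one comparator, says that the ratio will be reported if appropriate, and commits in general terms to good practice. The article is condensed, and a fuller economics plan may contain the comparison. What remains is that the one specific sentence names CAU, and the general commitment does not replace it. If a fuller plan does more, this sentence misdescribes it.

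Third, a reader might infer that the plan would lead to funding the dearer programme, or that ETPB is the dearer one because of its home visits. Neither is supported. The article states no threshold and no adoption rule, and MB's 16 group hours may outweigh ETPB's home visits.

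Fourth, the ETPB–MB point estimates can be obtained by subtracting the two sets of increments. That is true of the point estimates. Separate intervals against CAU do not give the joint uncertainty in costs and QALYs, because both contrasts share the CAU arm.

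**Conclusion.** The point holds as a limit of the stated comparator. ICERs against CAU can show whether each programme is worth adding to usual care. If both look acceptable, they do not show which is the better buy, and no such comparison is planned although the clinical analysis makes it.

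The consequence is possible, not certain. It arises only if both programmes pass against CAU and someone must choose between them. Its size depends on figures the article does not give. Of the six assumed sets, five give a conflict over some range of thresholds (£22,500 to £50,000 in set 1) and one gives none. The sets were chosen to show the mechanism, so that count is not a probability. The change is worth making because it improves on the stated method and uses data already planned.

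**What to change.** In the Economic Evaluation section, and in the matching sentence under Planned analysis, replace the comparison with CAU by a full incremental analysis of the three arms:
- order the arms by mean cost;
- remove dominated and extendedly dominated options;
- give each ICER against the next-best remaining option;
- report net monetary benefit for all three arms with their joint uncertainty.

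Keep the ICERs against CAU as supplementary results, since they answer the economic question as worded.

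The cost is slightly more analysis work. Resource use and EQ-5D are already to be collected in all three arms, so no new data and no change in sample size are needed.
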